### Inclusion criteria

Eligible participants will be women ages 45-69, with a body mass index of 28 to 45, who are residents in one of 10 rural counties in a midwestern state in the USA [26]. The potential pool of women classified as minority (predominantly of Hispanic origin) is < 1.6%. Other inclusion criteria include being able to: speak and read English, communicate over the phone, use a computer with minimal assistance to complete Internet surveys, walk without an assistive device or oxygen, have access to the Internet and a DVD player. Eligible women will be included if they answer "no" to all questions on the Physical Activity Readiness Questionnaire (PAR-Q) or obtain medical clearance from their physician to participate [42]. Women who have a BMI from 40-45 or who are diagnosed with Type II diabetes without requirements for insulin will be required to obtain medical clearance.

### Exclusion criteria

Women will be excluded if they are overweight with a BMI of 25-27.99 because they would reach normal weight with less than 5% loss, or if they have a BMI over 45, and thus may require a different approach to weight loss [26]. Women also will be excluded if they have a diagnosis of Type 1 diabetes or have a diagnosis with Type 2 diabetes and require insulin. Other exclusionary criteria include having a history of 10% or greater weight loss in the last six months, being enrolled currently in a weight loss management program or a formal program of cardiac or physical rehabilitation, taking medications that affect weight loss or weight gain, participating in current cancer treatment, or having any other physical or medical restrictions that would preclude following the recommendations for moderate physical activity and health eating.

### Participant recruitment and enrollment

A total of 306 women will be recruited over a 10 month period, during summer 2011 through spring 2012, from the 10 counties within 50 miles of the local community college where the assessments will be completed. Planned recruitment methods include speaking at community events and targeting potential participants using newspaper, radio and flyers posted in the community. Individual contacts will be made with local physicians asking them to refer overweight/obese women to the study. The recruiter will work closely with the county health department personnel who serve mostly low income and/or Hispanic populations to recruit persons with Hispanic backgrounds and persons of lower socioeconomic levels.

The recruiter will conduct a preliminary screening interview with potential participants to establish eligibility for the study and provide information for the informed consent process. The recruiter will provide contact information to the research nurses at the assessment office for each eligible woman who agrees to participate. These nurses will contact the women to verify if physician clearance was obtained, will schedule appointments to complete the consent process, and will begin baseline assessment if eligible.

### Baseline assessment

The baseline assessment will be conducted over 2 visits scheduled within 3 weeks. All other assessments will require one visit only. The research nurses will orient women to access the Women Weigh-In for Wellness website and instruct them on use of an accelerometer and a pedometer.

The women will be randomly assigned to one of 3 intervention groups upon completion of baseline assessment visit 2, using an allocation schedule previously created by the project statistician, who will not have any contact with the women during the trial. Each woman will receive notice of her randomization electronically at the first login after completing baseline visit 2. The research nurse will remain blinded to group assignment throughout the study.

### Interventions

#### Conceptual framework and background

The Health Promotion Model, with theoretical underpinnings in Social Cognitive Theory, was selected as a framework for the research to explain and modify the adoption and maintenance of healthy eating and activity behaviors needed for weight loss and maintenance in this study [43]. The Health Promotion Model emphasizes the active role of an individual in self-initiation and maintenance of health behaviors. Constructs selected from the model for use in the intervention design of this study are those for which there is empirical evidence supporting predictive validity for modifying behavior, including four behavior-specific cognitions (perceived benefits of action, barriers to action, self-efficacy and interpersonal influences) as well as commitment to a plan of action through goal setting. Prior work supports the association of these constructs with eating and activity behaviors among midlife and older rural women [44].

#### Intervention groups

All three theory-based interactive web-delivery intervention groups will receive the same content which provides a lifestyle change plan to accomplish their individual pound targets for a minimum of 5% and preferably 10% weight loss. The weight loss and maintenance approach will follow recommendations from the 2010 Dietary Guidelines for Americans [5], the 2008 Physical Activity Guidelines for Americans [3] and Healthy People 2010 [4]. The plan goals will be to achieve a weight loss of 1-2 pounds per week in the first 6 months by reducing caloric and fat intakes and gradually increasing physical activity to recommended levels. Caloric intakes will be reduced by 500-1000 kilocalories from baseline caloric needs, with a minimum caloric level established at 1200 kilocalories. Sedentary physical activity levels were assumed in calculating caloric needs.

To monitor and enhance the reliability and validity of our behavioral interventions, we developed an intervention fidelity plan described in Table 1, that addresses the design of the study, training of the interventionists, delivery of the intervention, receipt of the treatment by the participant, and enactment that ensures that the participant performs the skills and strategies as intended, based on Resnick's comprehensive model [45].

**Table 1 T1:** Women Weigh-In for Wellness Intervention Fidelity Plan.

Study Component	Fidelity Plan
Design	1. Ensure same intervention dose within conditions
	• Fixed content in internet web-messaging
	• Feedback about weight logs and eating activity goals provided at fixed intervals
	• Professional weight loss counseling provided using fixed length, frequency and number of contact sessions
	• Peer support group provided using fixed frequency and fixed content of discussion topics posted
	• Any deviations from protocol recorded
	2. Ensure equivalent dose across conditions
	• Web-messaging content identical across intervention groups
	• Frequency of additional contact for women in professional counseling email group and peer-led discussion group is similar
	3. Plan for implementation setbacks
	• Train back-up providers for professional weight loss counselor and peer support leader positions

Training	1. Training of all personnel by investigators initially and at specified intervals
	2. Guidelines for content of email messages and discussion board postings established

Intervention Delivery	1. Investigator-prepared guide for content/concepts in newsletters and hot topics
	2. Investigator oversight of newsletters and hot topics before website posting
	3. For professional weight loss counseling via email
	• Emails copied to and monitored by investigators
	• Email messages sent and received printed and filed weekly
	4. For peer-led online support group
	• List of topics prepared have oversight by investigators prior to testing
	• Project coordinator and/or investigators monitors discussion board weekly
	• Record of discussions printed and filed weekly

Intervention Receipt	1. Monitoring of all participants
	• Goal-setting forms
	• Weight logs
	• Weekly hits by each participant
	2. Monitoring of participants in peer-led online support group
	• Log-in
	• Postings
	3. Monitoring of professional weight loss counseling via email
	• Return receipt used to monitor opening of email messages
	• Replies from participants printed and filed

Enactment	1. Monitoring of behavioral skills and cognitive strategies of participants
	• Attainment of goals
	• Assessments of weight, and eating and activity behavioral and biomarkers
	• Assessments of cognitive-perceptual influences at 6,18, and 30 months

#### Phase 1 guided weight loss

New messages will be posted on the website each week for the first 6 months, and will remain available throughout the study. The women will receive an email with a preview of the content and a link to the site each time new content is posted. The messages will be targeted to midlife and older rural women and both an educational and a behavioral change approach will be used in the design of the messages. An eating and activity plan will provide content relevant to weight loss. Behavioral approaches will include self-monitoring tools, goal setting, individualized feedback regarding assessment results, relapse techniques, and motivational messages related to benefits of and barriers to action, self-efficacy, and interpersonal support. Interactive features such as quizzes, logs, and short games will be included as well as a resource area. Since self-monitoring is an important strategy in weight loss, women will be requested to post their eating and activity behaviors daily, and weights and goals weekly. Graphs of eating, activity, and body weight will be generated from the women's log entries to provide visual feedback to each woman about her progress.

A trained peer leader will facilitate an asynchronous discussion with those women enrolled in the interactive web-site plus peer counseling group. The peer leader will post a message once a week and participate in the discussion with the women about topics of interest relevant to the weekly messages. Because recruitment will occur over 10 months, the women will be placed in small discussion groupings based upon their time of enrollment. For intervention fidelity, the peer-led support discussion group will be monitored weekly by one of the investigators, and each woman's log-ins and postings will be tracked.

The interactive web-site plus professional email-counseling group will have their eating, activity and weight logs and goals on the website monitored by a professional counselor experienced in healthy eating and activity to accomplish weight loss. The counselor will send email feedback once a week using an email process following the 5A's Model for Behavioral Counseling (assess, advise, agree, assist and arrange) [46] that was adapted for this study. The women can email questions for the counselor to answer. The counselor will blind copy an assigned investigator on all emails and a return receipt will be issued to monitor women's opening of emails.

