### Sample size

Sample size needed for the study was estimated for a test of group difference in response averaged across time using generalized estimating equations [41]. Calculations assumed a group mean difference of .45 standard deviations based on median values on these outcomes in [12,15] and our pilot work, two measurement times per phase, within-subject correlation ≤ .5, and α of .017 (Bonferroni adjustment for three pairwise comparisons). For the most conservative pairwise test that will be conducted, the two-sided comparison of the groups receiving counseling, 76 participants will be needed in each group. A total sample size of 306 will be recruited to allow for attrition of 25%, consistent with that experienced in both published weight loss studies and our own pilot work.

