#### Data analysis

The primary analysis will focus on each phase separately, testing planned pairwise comparisons of the intervention groups over time using generalized estimating equations (GEE). The primary end point will be average change in outcome from the beginning of each phase. GEE also will be used to test whether the groups differ over time in the proportion of women meeting 5% and 10% weight loss goals. Secondary analyses will include a trend analysis of differences in the pattern of change across the entire 30 months of the study. All primary analyses will be consistent with the intent-to-treat principle and imputation of missing values may be undertaken, depending upon the extent and pattern of missing data.

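### Peer-arm women are treated in shared discussion groupings, but the sample size allows only for within-woman correlation and the planned GEE is not said to account for the grouping

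*Protocol article*

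**What the plan says.** The Phase 1 section describes a facilitated, asynchronous discussion for the peer arm. Because recruitment runs over 10 months, "the women will be placed in small discussion groupings based upon their time of enrollment". The Phase 2 section keeps the peer leader in the discussions to month 18. The Phase 3 section leaves the discussion area open to month 30 without the leader. The website-only arm has no discussion, and email feedback in the professional arm goes to each woman individually.

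The Sample size section sizes "a test of group difference in response averaged across time using generalized estimating equations". Its assumptions are these:
- Effect: "Calculations assumed a group mean difference of .45 standard deviations".
- Repeated measures: "two measurement times per phase, within-subject correlation ≤ .5".
- Significance level: "α of .017 (Bonferroni adjustment for three pairwise comparisons").

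For what it calls the most conservative test, "the two-sided comparison of the groups receiving counseling, 76 participants will be needed in each group". It then adds: "A total sample size of 306 will be recruited to allow for attrition of 25" per cent.

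The Data analysis section plans each phase separately, "testing planned pairwise comparisons of the intervention groups over time using generalized estimating equations (GEE"). It names neither the cluster unit of the GEE nor the discussion groupings. No ICC, grouping size, design effect or power figure appears in the article.

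**The concern.** This is an individually randomised trial with group treatment in one arm. What the peer arm adds to the website is interaction among the women who share a discussion. That mechanism can make outcomes within a grouping more alike than outcomes across groupings. Women in the other two arms share no such unit.

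Two consequences follow if the correlation is positive. First, 76 women in the peer arm carry less information than 76 independent women, so power is lower however the data are analysed. Second, an analysis that clusters only on the woman would understate the standard error and exceed the .017 level.

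Two of the three planned comparisons involve the peer arm. Peer v website is part of the stated hypothesis. Peer v professional bears on the possible financial savings raised in the Background, and it is also the comparison on which the sample size was based.

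**Working it through.** **Inputs from the Sample size section.** Difference 0.45 SD; two measures per phase; within-subject correlation ρ up to .5; two-sided α = .017, so z = 2.387; 76 per group; 25% attrition; 306 in total.

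**Assumed, because the article does not give them.** Power 80%; equal allocation (306/3 = 102 per arm); number of women per grouping m; ICC of the phase-averaged outcome.

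**1. Reproduce the plan's figure.** The mean of two measures has variance (1 + ρ)/2 = (1 + .5)/2 = .75 in SD² units.

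n per group = 2 × .75 × (2.387 + 0.842)² / .45² = 77.2, that is 78, against the stated 76. With ρ = .45 the result is 75.

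Power at 76 per group: the SE is √(2 × .75/76) = .1405, and Φ(.45/.1405 − 2.387) = 79.3%.

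Attrition: 76/.75 = 101.3, rounded up to 102, and 3 × 102 = 306.

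The stated figures therefore follow from within-subject correlation alone. At ρ = .5 they leave no room for a design effect.

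**2. Add clustering in the peer arm only.**
- Design effect in the peer arm: DE = 1 + (m − 1) × ICC
- Variance ratio of a peer-arm contrast: v = (1 + DE)/2
- Actual two-sided error if the analysis ignores grouping: 2 × [1 − Φ(2.387/√v)]
- Power if the analysis uses the correct standard error: Φ(.45/√(2 × .75 × v/76) − 2.387)

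**3. Choose a grouping size.** About 102 peer-arm women over 10 months is roughly 10 a month. If groupings were monthly, each would enrol about 10 women. Since 76 is the number after attrition, the matching size is 10 × .75 = 7.5 completers.

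**4. Results with ρ = .5.**

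| Women per grouping analysed | ICC | DE | v | SE ratio √v | Error if ignored | Power if handled |
|---|---|---|---|---|---|---|
| any | 0 | 1 | 1 | 1 | .017 | 79% |
| 5 | .01 | 1.04 | 1.02 | 1.01 | .018 | 78% |
| 7.5 | .05 | 1.325 | 1.1625 | 1.08 | .027 | 72% |
| 7.5 | .10 | 1.65 | 1.325 | 1.15 | .038 | 65% |

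For the third row: DE = 1 + 6.5 × .05 = 1.325 and v = 2.325/2 = 1.1625. The error is 2 × [1 − Φ(2.387/1.078)] = .027. The SE is √(1.5 × 1.1625/76) = .1515, and Φ(.45/.1515 − 2.387) = 72%.

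**5. Sensitivity to ρ.** The article gives .5 as an upper limit. At ρ = .3 the variance is .65. Unclustered power at 76 is then 85%, and with 7.5 per grouping and ICC .05 it is 79%. The error column does not depend on ρ.

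All figures use the normal approximation. With only about 10 groupings in the peer arm, limited degrees of freedom would lower power somewhat further.

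**The case against.** A reader might infer that the planned GEE is wrong and that its standard errors are too small. The article does not support that. The Data analysis section names no cluster unit, so a GEE clustered on discussion grouping would be compatible with its wording, and a condensed article may leave that detail to a fuller document. Analysis at the level of the woman is only an inference from the Sample size section. This objection stands, and the statement about standard errors must stay conditional.

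The ICC is also unknown and could be small. Topics and posting frequency are fixed in the fidelity plan, the text speaks of one trained peer leader, all arms receive the same web content, and the leader withdraws in phase 3. These features may lower the ICC, and lower it differently by phase. However, they standardise what is posted rather than how members respond to one another, so they do not make the ICC zero.

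Season of enrolment is a weak argument for clustering. All three arms enrol over the same 10 months, so a calendar effect is largely shared and would mostly cancel in the contrast. The case rests on shared discussion alone.

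What the objection does not reach is the sample size. Its assumptions are listed and its result reproduces without any between-woman correlation. A later analysis plan can correct a standard error, but it cannot restore power that 306 women do not provide.

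**Conclusion.** The point holds in a limited form. The firm part is that the trial creates clusters in one arm and sizes the comparisons of that arm as if the women were independent. Given a positive ICC, power for peer v website and peer v professional is below what 76 per group implies. The conditional part is that type I error exceeds .017 only if the ICC is positive and the analysis ignores the grouping.

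The size runs from negligible (error .018, power 78%) to material (error .038, power 65%) over the assumptions tabulated above. The middle case is about .027 and 72%. These figures rest on an assumed ICC and grouping size, ρ at its stated upper limit, and an implied power of about 79% that the article does not itself state. Professional v website is unaffected.

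**What to change.** - Record each peer-arm woman's discussion grouping as an analysis variable. The trial already forms these groupings and tracks log-ins and postings, so membership should be available.
- State that discussion grouping is the cluster unit in the peer arm, with women in the other two arms as singletons. Use either a partially nested mixed model, with a grouping random effect in the peer arm only and Satterthwaite-type degrees of freedom, or GEE clustered in that way with a small-sample sandwich correction. Repeated measures within a woman must still be accounted for.
- Give the intended grouping size, and restate power for the two peer-arm comparisons over a stated range of ICC and grouping size. More women need not be enrolled.

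The cost is some analysis wording and one variable. Intervals for the peer-arm comparisons will be wider and their stated power lower, slightly so if the ICC is near zero and noticeably so at an ICC of .05 to .10.

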#### Phase 2 guided continuing weight loss/maintenance

The purpose of phase 2 will be to promote continued weight loss for those women who have not lost at least 10% of their baseline weight and to promote maintenance of that loss for those women achieving a 10% weight loss. The activity target will increase to a minimum of 60-90 minutes per day consistent with current guidelines [47,48].

At the 6-month assessment, women in all groups will be given an investigator-produced DVD [Banding Together for Strength] with 2 latex-free resistive bands to assist them in starting or continuing resistance training in the convenience of their own homes. The DVD uses age appropriate exercises led by age-related role models in order to enhance self-efficacy for resistance training. The women will have access to all Internet messages received in phase 1 for their review. Phase 2 new messages will focus on hot topics in the form of a news brief posted every week in months 7-9, every 2 weeks in months 10-13, and monthly in months 14-18. Content will focus on timely articles based on the literature with an emphasis on women taking more responsibility for their weight and moving toward permanent lifestyle change. Women will be asked to continue posting weights weekly and goals every two weeks.

The peer-led support group will receive a posted message for the discussion board from the peer leader weekly in months 7-9, every 2 weeks in months 10-13 and monthly in months 14-18. The peer leader will continue to participate in weekly discussions and will encourage the women to continue to discuss issues related to weight loss.

The group receiving professional email-counseling will have their postings of weight, activity, food, and goals reviewed weekly in months 7-9, every two weeks in months 10-13 and monthly in months 14-18. The counselor will send one reminder email each time that a woman has not posted as requested and the counselor will continue to respond to email questions from women throughout phase 2.

#### Phase 3 self directed weight maintenance

The purpose of phase 3 is to move women toward independence. Less support will be given, but sites to post eating, activity, goals and weight will be available. The target will be prevention of weight regain, with encouragement provided to the women to maintain their 5% to 10% weight loss by using the skills they have developed. The goal is for women to have made permanent lifestyle changes by the end of phase 3.

All three interactive-website intervention groups will have access to a content library on the website with hyperlinks to web-based resources intended to foster a reliable method of self-directed learning. Carefully selected articles related to healthy eating, activity, weight loss and weight maintenance will be organized into subject folders on the website for ease of participant access. Women will be encouraged to post weekly weight, and set/revise goals every two weeks.

Women assigned to the website plus peer-lead support group will have access to the discussion area but there will be no participation or postings by the peer leader.

Women assigned to the website plus professional email-counseling group will receive responses from the professional counselor to individual women's emailed questions; however, the counselor will not be providing feedback on the weight, eating, activity or goal setting logs.

